**Methods/Design:**

A randomized, parallel, single-center, assessor- and statistician-blinded, controlled clinical trial will be performed. A total of 100 teenagers, between seven and 12 years of age, with mild-to-moderate myopia and spherical lenses <-6.00 D and cylindrical lenses <-1.50 D will be selected from the Xinjiang Uygur Autonomous Region Institute of Traditional Chinese Medicine, a grade III level A teaching hospital in Urumqi, Xinjiang, China (Xinjiang Medical University Affiliated Hospital of Traditional Medicine). The subjects will be randomly assigned to two different groups (control and acupuncture groups), each group containing 50 subjects. The subjects in both groups wear single-vision corrective lenses. In the acupuncture group, acupuncture will be performed daily for nine consecutive days on five points (bilateral Cuanzhu, Tongziliao, Sibai, Muchuang, and Hegu), followed by no treatment for one day. Six cycles of treatment will be undertaken continuously for a total of 60 days. Following 60 days of treatment, a follow-up period of six months will be included. The primary outcome will be diopter determination. The secondary outcomes will include distance visual acuity, axial length, lens thickness, ciliary body thickness, and subjective symptoms of the eyes and entire body. The main time points for the evaluation of clinical efficacy will be the first, third, and sixth months after treatment.

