### Primary outcome

The primary outcome in this trial will be diopter measurement
[21]. After mydriasis using cyclopentolate hydrochloride eye drops (15 ml; Alcon-Couvreur, Puurs, Belgium), a comprehensive refractometer (AOS-1,500; Nidek, Aichi, Japan) will be used to conduct objective optometry (computer optometry and retinoscopy), then subjective optometrics. Subjective optometrics will be divided into the following two parts: optometrics will be conducted on a single eye (the right eye followed by the left eye), and a bilateral eye balance examination. Subjective optometrics of a single eye will be divided into the following three stages: the initial maximum plus the maximum visual acuity (MPMVA) will be identified, Jackson cross cylindrical lenses will be used to determine the axial direction and degree of the cylindrical lens, and the MPMVA will be repeated. The results will be recorded after optometrics. When the pupils recover, a re-examination will be carried out (three days after the use of cyclopentolate hydrochloride eye drops). After re-examination, the glasses will be tried again. The degree of the glasses will be marked on the glass trial frame, to be chosen by the subjects based on subjective judgment. Finally, the diopter of the glasses and prescription glasses will be determined. The optometrist will not participate in other parts of the trial. The main time points for evaluation of clinical efficacy will be the first, third, and sixth months after two months of treatment.

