### Secondary outcomes

The secondary outcomes in this study will include distance visual acuity
[22], AL
[17], lens thickness
[18], and ciliary body thickness
[19]. These indices will be measured before treatment, and at the first, third, and sixth months after two months of treatment. The objective examinations will be recorded in the CRFs. The main time points of evaluation will be the sixth month after treatment or when the trial is terminated.

Distance visual acuity will be measured using a standard logarithmic visual acuity test chart (TR-B; Tongrui Medical Equipment Co., Ltd., Tianjin, China), under sufficient lighting to measure the parameters of visual acuity, with a 5-m distance to the visual acuity test chart. All visual acuity examinations in this study will be carried out by one nurse in a fixed place who will not participate in acupuncture treatment or clinical examinations. The specific details of the subjects will not be disclosed to the nurse.

In order to measure AL and lens thicknesses, the subject will be placed in the supine position. Oxybuprocaine Hydrochloride Eye Drops (20 ml, Santen Pharmaceutical Co. Ltd. Suzhou, China) will be applied to the eye to be examined, and topical anesthesia will be applied. The subjects will be asked to watch the red light at the top of the probe with the eye to be examined. A disinfected ultrasound probe will be placed on the surface of the cornea. Sound waves will pass through the middle of the corneal vertex, the center of the lens, and the vitreous body, to reach the macular fovea. The sound beam will be kept in a vertical orientation. The AL and lens thicknesses will be measured. Ten sets of values will be selected, with a measurement error within 0.1 mm
[22]. The lens thickness is the axial distance from the front surface to the posterior surface of the lens
[19, 23]. An ophthalmic ultrasound instrument (CINESCAN; Quantal Medical, Paris, France) will be used for these measurements in the proposed study. Ten measurements of a particular index will usually be made, and these 10 measurements will be recorded and the average value obtained. The AL and lens thickness measurements will be carried out by one full-time physician, on a fixed instrument, and at a fixed location. The physician will not participate in visual acuity examinations and acupuncture treatment, and the specific details with respect to the grouping of subjects will not be disclosed to the physician.

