### Statistical analysis

All statistical analyses will be performed using SPSS 17.0 statistics software. For quantitative data, the distribution pattern and homogeneity of variance will be examined. If there is a symmetric distribution, the mean (M) ± standard deviation will be used for statistical description, otherwise the M interquartile range (IQR) will be used to describe the trend of concentration and amount of scatter. If this condition is met, the Student's t-test will be used to compare the differences between the quantitative indices between the groups, otherwise the Wilcoxon rank-sum test will be used. For categorical data (binary classification and multiple classification), the composition ratio will be used for statistical description. Based on the observation of a theoretical frequency distribution, the χ^2^ or Fisher's exact test will be used, depending on the specific situation. The ranked data will be analyzed using the Wilcoxon rank-sum test.

Primary and secondary outcomes will be analyzed by the superiority test in accordance with the principle of intention-to-treat, using Per Protocol Set (PPS) and Full Analysis Set (FAS) datasets. The indices of safety evaluation will be analyzed using the Save Set (SS) dataset. The significance level in this study will be set at α = 0.05, and the one-sided test will be used. The detailed statistical analytical methods for primary and secondary outcomes and baseline data are shown in Table 
2 (variables, measures, and methods of analysis).

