**Table 2 Tab2:** **Variables, measures, and methods of analysis**

Variable/outcome	Hypothesis	Outcome measure	Methods of analysis
1) Primary	Intervention improved outcome from baseline to 7 days	Adherence% (>80%) [binary]	
Diopter	Diopter reduced or increased after treatment	Diopter [continuous]	t-test (rank-sum test) or repeated measurement
2) Secondary	Intervention improved outcome from baseline to 7 days	Adherence% (>80%) [binary]	
Visual acuity	Visual acuity did not increase or decrease after treatment	Visual acuity changes [continuous]	t-test (rank-sum test) or repeated measurement
Axial length	Axial length was not increased	Axial length changes [continuous]	t-test (rank-sum test) or repeated measurement
Lens thickness	Lens thickness was not increased	Lens thickness changes [continuous]	t-test (rank-sum test) or repeated measurement
Ciliary body thickness	Ciliary body thickness was not increased	Ciliary body thickness changes [continuous]	t-test (rank-sum test) or repeated measurement
Eye symptoms and systemic symptoms	No adverse symptoms	No adverse symptoms	Chi-squared test or Fisher’s exact test
Compliance	Compliance	Cure rate [binary]	Chi-squared test or Fisher’s exact test
Combination therapy/treatment	Improvement occurred	Whether other drugs were used during treatment [binary]	Chi-squared test or Fisher’s exact test
Adverse event	Improvement occurred	Presence of drug-related adverse event [binary]	Chi-squared test or Fisher’s exact test
3) Baseline analyses:		Adherence% (>80%) [continuous]	
Age		CRF [continuous]	t-test (rank-sum test)
Weight and height		CRF [continuous]	t-test (rank-sum test)
Female versus male		CRF [binary]	Chi-squared test or Fisher’s exact test
Race		CRF [more categories]	Chi-squared test or rank-sum test
Birth weight		CRF [continuous]	t-test (rank-sum test)
Preterm children		CRF [binary]	Chi-squared test or Fisher’s exact test
Parental myopia or not		CRF [binary]	Chi-squared test or Fisher’s exact test
Sibling myopia or not		CRF [binary]	Chi-squared test or Fisher’s exact test
Daily close reading time		CRF [continuous]	t-test (rank-sum test)
Outdoor time		CRF [continuous]	t-test (rank-sum test)
Eye exercises every day or not		CRF [binary]	Chi-squared test or Fisher’s exact test
Daily sleep time		CRF [continuous]	t-test (rank-sum test)
Room light conditions		CRF [binary]	Chi-squared test or Fisher’s exact test
Poor reading habits		CRF [more categories]	Chi-squared test or rank-sum test

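### The primary outcome has three unranked main time points and an open choice between a single-visit test and repeated measurement, with no rule dividing the one-sided 0.05, and Table 2 adds a conflicting 7-day time frame

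*Protocol article*

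**What the plan says.** - **Outcome.** The Primary outcome section states: "The primary outcome in this trial will be diopter measurement". It attaches no summary measure and no single visit to it.
- **Time points.** The same section continues: "The main time points for evaluation of clinical efficacy will be the first, third, and sixth months after two months of treatment". The Abstract agrees: "The main time points for the evaluation of clinical efficacy will be the first, third, and sixth months after treatment".
- **Schedule.** Table 1 has diopter at baseline and at months 3, 5 and 8 only. With two months of treatment these are months 1, 3 and 6 afterwards (2 + 1, 2 + 3, 2 + 6). The only 7-day entry in Table 1 is the baseline column, at day -7.
- **Table 2, heading rows.** The rows that introduce the primary and the secondary outcomes both read "Intervention improved outcome from baseline to 7 days", with adherence above 80% in the outcome-measure column and nothing in the method column.
- **Table 2, diopter row.** Its hypothesis allows diopter to go either way after treatment. Its measure is diopter as a continuous variable, and its method is "t-test (rank-sum test) or repeated measurement".
- **Test and level.** The Statistical analysis section examines distribution and homogeneity of variance. If the condition holds, the t-test is used; "otherwise the Wilcoxon rank-sum test will be used". The section promises a superiority test on both the full analysis and per-protocol sets, one-sided at 0.05. It does not mention repeated measurement, a primary visit or any division of the 0.05.
- **Secondary outcomes.** That section says: "The main time points of evaluation will be the sixth month after treatment or when the trial is terminated".

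**The concern.** A confirmatory trial needs one comparison, fixed in advance, that decides whether it succeeded. Here three visits have equal standing, and two kinds of analysis that answer different questions (a difference at one visit, or a difference across visits) are offered with no rule for choosing. With no hierarchy and no split of the significance level, a favourable visit or method could be picked after the data are seen, and the nominal 5% would then not describe the real risk of a false claim.

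Table 2, where a reader would look to settle the matter, adds a fourth time frame at which no diopter is measured. Its hypotheses also do not match the promised superiority test. The diopter row has no direction although the test is one-sided, and secondary rows such as "Axial length was not increased" describe absence of change rather than a difference between groups.

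**Working it through.** **1. The time frames side by side.**

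| Place | Time frame |
|---|---|
| Abstract; Primary outcome | Months 1, 3 and 6 after treatment, unranked |
| Table 1 | Diopter at baseline and at months 3, 5 and 8 (the same three times) |
| Table 2, heading rows | Baseline to 7 days |
| Secondary outcomes | Month 6 after treatment, or termination; secondary outcomes only |

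The Abstract, the Primary outcome section and Table 1 agree with one another. The 7-day entry agrees with none of them.

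**2. Which choices are open.** The choice between t-test and rank-sum test follows a stated distribution rule. The choice between a single-visit test and repeated measurement has no rule. Nor is there one for which visit counts, or for whether one visit or all three must succeed.

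**3. Error rate if any visit may count.** The inputs are three visits (Primary outcome) and one-sided 0.05, critical value 1.645 (Statistical analysis). The correlation ρ between visits is an assumption, because the document gives none. The plan's own figure is the nominal 0.05. A simulation of a single-visit t-test with 40 children per arm (50 less the expected 20% dropout) and 20,000 runs returned 0.0495 to 0.0517 across the correlations tried, so that figure is reproduced for one test.

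- Independent visits: 1 − 0.95³ = 0.143. This is the ceiling for visits that are not negatively correlated.
- Equally correlated visits: P(at least one z > 1.645) = 1 − ∫ φ(u) Φ[(1.645 − √ρ·u)/√(1 − ρ)]³ du.

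| Assumed ρ | Any of three visits (formula) | Any of three visits (simulated t-tests) | All three visits required (formula) |
|---|---|---|---|
| 0.5 | 0.1184 | 0.1208 | 0.0050 |
| 0.7 | 0.1027 | 0.1035 | 0.0115 |
| 0.8 | 0.0926 | 0.0956 | 0.0168 |
| 0.9 | 0.0795 | 0.0810 | 0.0251 |
| 0.95 | 0.0705 | 0.0707 | 0.0318 |

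**4. Error rate if the visit is fixed but the method stays open.** Take month 6 as the visit and let either the single-visit test or the group contrast averaged over the three visits count; the average stands in for repeated measurement. The two statistics correlate at √((1 + 2ρ)/3), which is 0.8165 at ρ = 0.5 and 0.9832 at ρ = 0.95. The chance that at least one exceeds 1.645 under the null is then 0.0742 and 0.0575 respectively; the simulation gave 0.0766 and 0.0579. Fixing the visit without fixing the method therefore leaves a smaller excess.

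**5. Error rate with one contrast.** A single named contrast at one-sided 0.05 has a false-positive rate of 0.05.

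**The case against.** The strongest reply is that the document never says a win at any one visit is success. It names times for evaluation, not three separate tests. One repeated-measures contrast, which Table 2 permits, would not inflate the error, and requiring all three visits would push it below 5%. This stands as far as it goes: the inflation depends on a success rule that the text leaves open. It does not remove the problem, because the document states neither protective rule. Nor is this just detail left to an analysis plan, since the article itself prints time frames that conflict and methods offered as alternatives.

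A reader might infer several stronger points that the documents do not support:

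- *Three tests to choose from freely.* The Statistical analysis section has a rule for t-test versus rank-sum test. Only single-visit test versus repeated measurement is open.
- *A primary hypothesis that cannot be evaluated.* The 7-day and adherence entries sit on heading rows with no method. The adherence entry also appears on the baseline heading row, where it cannot be an outcome. This looks like leftover template text. The diopter row below has its own hypothesis, measure and method; it is loosely worded but can be evaluated.
- *A false-positive rate of 14.3%.* That needs independent visits, which is implausible for repeated refraction of the same children over five months.
- *Month 6 as the primary time already.* The sentence that singles it out belongs to the secondary outcomes and adds termination as an alternative.
- *Non-significance to be read as proof of no change.* Nothing says so. The Statistical analysis section compares groups, and Table 2 lists changes as the measures for the visual acuity, axial length, lens and ciliary body rows. The secondary hypotheses need rewording; they do not show an invalid test.

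**Conclusion.** The point holds in this form: the plan does not fix the visit or the method that decides the primary comparison, it does not protect the one-sided 0.05 across the options it leaves open, and Table 2 contradicts the text and the schedule on timing.

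The size is conditional. On an any-visit reading, with correlations between 0.95 and 0.5, the false-positive rate is about 7% to 12% instead of 5%. With month 6 fixed and only the method open it is about 6% to 7%. The correlations are assumptions, and the any-visit rule is a reading that the text allows but does not state. The documents therefore establish an undefined success criterion. They do not establish that the trial's error rate is inflated.

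It should be corrected before outcome data accumulate, because until then the plan does not say what result would count as success.

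**What to change.** 1. Name one primary comparison: the between-group difference in change in diopter from baseline at one visit. Month 6 after treatment is a natural candidate. It is the last scheduled visit (month 8 in Table 1) and fits the Abstract's aim of judging efficacy over six months.
2. Name one method for it, for example a repeated-measures model using all three follow-up visits with the month 6 group contrast as the test. A different single contrast would also control the error, provided it is fixed in advance.
3. Make months 1 and 3 secondary.
4. In Table 2, remove or correct the 7-day and adherence entries on the heading rows. Reword the diopter hypothesis, with a direction, and the secondary outcome hypotheses as between-group differences in change, to match the superiority test.

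The cost is wording in Table 2 and in the Primary outcome and Statistical analysis sections, with no extra visits or measurements. The real concession is that a positive result at month 1 or 3 alone would no longer count as trial success. The Trial status section reports six participants recruited at the time of writing, so the change was feasible early.

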### Secondary outcomes

The secondary outcomes in this study will include distance visual acuity
[22], AL
[17], lens thickness
[18], and ciliary body thickness
[19]. These indices will be measured before treatment, and at the first, third, and sixth months after two months of treatment. The objective examinations will be recorded in the CRFs. The main time points of evaluation will be the sixth month after treatment or when the trial is terminated.

Distance visual acuity will be measured using a standard logarithmic visual acuity test chart (TR-B; Tongrui Medical Equipment Co., Ltd., Tianjin, China), under sufficient lighting to measure the parameters of visual acuity, with a 5-m distance to the visual acuity test chart. All visual acuity examinations in this study will be carried out by one nurse in a fixed place who will not participate in acupuncture treatment or clinical examinations. The specific details of the subjects will not be disclosed to the nurse.

In order to measure AL and lens thicknesses, the subject will be placed in the supine position. Oxybuprocaine Hydrochloride Eye Drops (20 ml, Santen Pharmaceutical Co. Ltd. Suzhou, China) will be applied to the eye to be examined, and topical anesthesia will be applied. The subjects will be asked to watch the red light at the top of the probe with the eye to be examined. A disinfected ultrasound probe will be placed on the surface of the cornea. Sound waves will pass through the middle of the corneal vertex, the center of the lens, and the vitreous body, to reach the macular fovea. The sound beam will be kept in a vertical orientation. The AL and lens thicknesses will be measured. Ten sets of values will be selected, with a measurement error within 0.1 mm
[22]. The lens thickness is the axial distance from the front surface to the posterior surface of the lens
[19, 23]. An ophthalmic ultrasound instrument (CINESCAN; Quantal Medical, Paris, France) will be used for these measurements in the proposed study. Ten measurements of a particular index will usually be made, and these 10 measurements will be recorded and the average value obtained. The AL and lens thickness measurements will be carried out by one full-time physician, on a fixed instrument, and at a fixed location. The physician will not participate in visual acuity examinations and acupuncture treatment, and the specific details with respect to the grouping of subjects will not be disclosed to the physician.

In order to measure ciliary body thickness, oxybuprocaine hydrochloride eye drops will be applied to the eye to be examined. After topical anesthesia is applied, a disinfected eye cup of appropriate size will be placed beneath the upper eyelid. At this time, the subjects will be asked to move the eye downward to prevent scratching the cornea. The lower eyelid will then be pulled. The eye cup will be placed beneath the lower eyelid, so that it is immobilized between the eyelids and the eyeball. Distilled water will be poured into the eye cup. The contralateral eye will gaze at the red indicator light on the nasal side. An ultrasound biomicroscope (MD-300 L; Meda Co. Ltd., Tianjin, China) will be used. A 50 mhz transducer with 4 to 5 mm tissue penetration depth will be used to measure ciliary body thickness at the temporal corneoscleral limbus of the eye to be examined. The image will then be obtained. The built-in ruler will be used to measure ciliary body thickness (vertical distance) 2 mm behind the scleral spur
[24, 25]. The position of the bilateral temporal side (nine points in the right eye, three points in the left eye) will be measured once manually and the results will be recorded. The same instrument will be used for all measurements. The measurement of ciliary body thickness in this research will be completed by one full-time physician, using a fixed instrument, in a fixed place. The physician will not participate in visual acuity examinations or acupuncture treatment, and the specific details of the subjects will not be disclosed to the physician.

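### Ciliary body thickness rests on one manual ruler reading per eye per visit; averaging three readings would be a cheap gain in precision (minor)

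*Protocol article*

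**What the plan says.** All of this is in the protocol article, section Secondary outcomes, unless another place is named.

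- **Site.** The ultrasound biomicroscope is used to "measure ciliary body thickness at the temporal corneoscleral limbus of the eye to be examined". The level is then fixed: "The built-in ruler will be used to measure ciliary body thickness (vertical distance) 2 mm behind the scleral spur".
- **Position and number of readings.** The text then names the position on the temporal side of both eyes, with a bracket that runs on into the number of readings: "nine points in the right eye, three points in the left eye) will be measured once manually and the results will be recorded".
- **Standardisation.** The measurement "will be completed by one full-time physician, using a fixed instrument, in a fixed place". The physician takes no part in acupuncture or visual acuity testing and is not given the subjects' details.
- **Neighbouring measures.** For axial length and lens thickness, "these 10 measurements will be recorded and the average value obtained".
- **Timing and analysis.** Table 1 schedules ciliary body thickness at baseline and at three follow-up visits. Table 2 lists it as a change on a continuous scale, compared by t-test, rank-sum test or repeated measurement.

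**The concern.** The reader of the image has to find the scleral spur, mark off 2 mm from it and set the ruler across the ciliary body, all by hand. Each step adds random within-reader error. The protocol prescribes one such reading, so none of that error is averaged out. Because the outcome is a change, the error enters twice, once at baseline and once at follow-up.

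What is at stake is the precision of a secondary outcome. The Background and Discussion give this outcome some weight. They name ciliary body thickness among the objective, quantitative indices chosen to limit bias, in a trial without a sham group. A noisier change score means a wider confidence interval and lower power to show a difference in this index if there is one.

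**Working it through.** **No figure to reproduce.** The sample size section concerns diopter and does not enter here. The documents give no repeatability figure for ciliary body thickness, so the size can only be shown over a range of assumptions.

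**Inputs**

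| Input | Value | Source |
|---|---|---|
| Ciliary body readings per eye per visit | 1, manual | Secondary outcomes |
| Axial length and lens thickness readings | 10, averaged | Secondary outcomes |
| Outcome analysed | change | Table 2 |
| s, SD of true change | not given | assumption |
| e, SD of one reading (placement error) | not given | assumption, 0.1s to 1.0s |

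**Formula.** If placement errors are independent between readings and visits, and k readings are averaged at each visit, then

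Var(change) = s² + 2e²/k.

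With k = 1 this is s² + 2e². With k = 3 it is s² + 2e²/3.

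**Results, in units of s²**

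| e | One reading | Mean of three | Reduction in variance |
|---|---|---|---|
| 0.1s | 1 + 2(0.01) = 1.020 | 1 + 0.02/3 = 1.007 | 0.013/1.020 = 1.3% |
| 0.2s | 1 + 2(0.04) = 1.080 | 1 + 0.08/3 = 1.027 | 0.053/1.080 = 4.9% |
| 0.5s | 1 + 2(0.25) = 1.500 | 1 + 0.50/3 = 1.167 | 0.333/1.500 = 22% |
| 1.0s | 1 + 2(1) = 3.000 | 1 + 2/3 = 1.667 | 1.333/3.000 = 44% |

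The number of subjects needed for a given precision is proportional to this variance. One reading instead of three therefore costs a factor of 1.020/1.007 = 1.01, 1.080/1.027 = 1.05, 1.500/1.167 = 1.29 or 3.000/1.667 = 1.80.

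**Why these are upper bounds.**

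- *Acquisition error.* Let a be the SD of error from probe position and angle at each visit. It adds 2a² to both columns, and re-reading the image does not touch it. With e = a = 0.5s, the variance goes from 1 + 0.5 + 0.5 = 2.000 to 1 + 0.5 + 0.167 = 1.667. The reduction is 17%, not 22%.
- *Repeated misplacement.* If placements on the same image have error correlation ρ, the mean of three has error variance e²(1 + 2ρ)/3. With e = 0.5s and ρ = 0.5, the variance goes from 1.500 to 1 + 2(0.25)(2/3) = 1.333. The reduction is 11%.

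**Direction of the effect.** If the error has the same distribution in both arms, which blinding of the physician supports, its expected contribution cancels in the difference between arm means. The expected difference is unchanged; its standard error and the power are what suffer.

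**Nine and three.** The bracket qualifies a position on the temporal side, not a quantity. Facing the subject, the temporal side lies at 9 o'clock in the right eye and 3 o'clock in the left. Read so, the bracket restates the temporal site already named, and the plan is one site and one reading per eye.

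**The case against.** **Preference rather than error.** Ten averaged readings are prescribed for a different procedure, with a probe held on the cornea and the beam aligned through the eye. That ten are wanted there does not show that one reading on an acquired image is inadequate. The method is cited to sources not available here, and the site, physician, instrument and place are all fixed. This stands as far as it goes: the documents do not show that one reading is unacceptable. But a single physician and a fixed instrument limit variation between operators and devices. They do not reduce the random error of one person's placements, which is what averaging addresses.

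**The gain may be negligible.** If e is 0.2s or less, the reduction is about 5% at most. This stands, and it is why the full range is shown.

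**Both eyes are measured.** True, and if the eyes are combined, some error is averaged already. The same formula then applies with s and e defined for the combined value.

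**Stronger readings that the documents do not support.**

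- A reader might infer that nine sites in the right eye and three in the left contradict the single temporal site. The bracket describes a location, and the numbers match the temporal clock hours. A count of nine or three would also not fit a measurement made once. This is a slip of wording.
- A reader might infer that the error dilutes or biases the treatment difference. Non-differential random error in a continuous outcome does not shift the expected mean difference.
- A reader might infer that this outcome is the least replicated of all. The section states no replicate readings for distance visual acuity either.

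**Conclusion.** The point holds as a minor one. The protocol affirmatively fixes one manual reading per eye per visit for an outcome that depends on hand placement and is analysed as a change, while two neighbouring outcomes are averaged over ten readings. The consequence is lost precision and power in one secondary outcome, without bias in the mean difference.

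The size is unknown. Averaging three readings would reduce the variance of the change by about 1% to 44% for e from 0.1s to 1.0s. This assumes independent placement errors and no acquisition error; relaxing either lowers the figure. The primary outcome is not affected, and the site definition is not contradictory.

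**What to change.** 1. **Readings.** State that the ultrasound image is saved. Have the same blinded physician make three independent ruler placements on it, finding the scleral spur afresh each time. Record all three values and analyse their mean, at baseline and at every follow-up visit.
2. **Wording.** Change the bracket to give the 9 o'clock position in the right eye and the 3 o'clock position in the left eye. This is a correction of language only.

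The cost is a few minutes of reading time per visit and saving an image that is already acquired; the article says that the image is obtained but not that it is kept. No further scan, staff or burden on the child is needed. Trial status reports six participants recruited out of the planned 100, so the change could cover nearly the whole trial. Images of those six can be re-read where they were saved. Where they were not, keep the single reading and document it.
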